### Participant adherence

Individual participation in each exercise session (both land and aquatic) will be recorded by the physiotherapist responsible for the intervention with a “0" if the participant does not attend or a “1" if the participant is present and participates. Strategies will be adopted to promote adherence to the exercises, including text messages and/or email [93]. If a participant misses two consecutive sessions, he/she will be contacted to resume the exercise sessions, as lack of adherence may affect the results obtained [94]. At the end of the interventions, participants who do not achieve at least 80% of the total sessions will be excluded from data analysis [91,95].

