### Intervention

The intervention will take place over 8 weeks at the Municipal Pool of Paião, located in Figueira da Foz, Portugal. The AG will conduct the aquatic exercise program, while the ALG will carry out both aquatic and land-based exercise programs. The intervention will begin after a one-week washout period, during which participants will cease any additional physical exercise, which they will maintain throughout the intervention weeks.

To monitor the intensity of the interventions, Borg CR-10 scale will be used. This is a tool to rate dyspnea and/or perceived exertion (RPE) experienced by an individual. The scale consists of a numerical list with 10 points (0–10), an adaptation of the original scale (6–20), that assesses and monitors the intensity/severity of shortness of breath/fatigue. Its use requires explaining that “0" means not experiencing dyspnea/fatigue at the moment and that “10" means the worst dyspnea/fatigue they have ever experienced or the worst imaginable dyspnea/fatigue [57,58]. This instrument will not be used during the assessment moments before and after the exercise programs but only to monitor the intensity during the sessions of both aquatic and land-based exercise programs. This scale is validated for monitoring dyspnea and fatigue, showing an excellent correlation with heart rate (r=0.92) and VO2 (*r*=0.92–0.93) and moderate reliability (ICC=0.50–0.66) [59].

Participants will be encouraged to maintain their daily activities as usual outside of the study. The participants may not participate in any other exercise programs.

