#### Aquatic-exercise program.

This intervention will consist of an aquatic-exercise program (Table 1), administered by a physiotherapist. It will include 16 sessions, twice a week, over 8 weeks at a water temperature between 32–34 ∘ C. Each session will be conducted in groups of 8–12 patients and will last about 45 minutes. The aquatic exercise sessions will include a warm-up phase (5 minutes): walking forwards, sideways, and backwards; a training phase (35 minutes): active range of motion exercises (10 minutes) for the spine, upper and lower limbs; aerobic exercises (5 minutes) with jumps and static running at various speeds; muscle strengthening (10–15 minutes), (8–12 repetitions), 1–2 sets, 8–10 exercises including hip flexion, extension, adduction, and abduction, knee flexion and extension, knee cycling, shoulder flexion, extension, and abduction, elbow flexion, extension, and pronation-supination, squatting, and stretching exercises (5–10 minutes) for the neck, trunk, and limbs; and a relaxation/cool-down phase (5 minutes): including lying supine and low-impact exercises such as slow walking, squatting, and standing [20,37,38,41,42]. For participants who cannot complete any exercise due to difficulty or discomfort, a modified version of each exercise will be offered. The load progression will be managed using auxiliary equipment, including flotation devices, plates, balls, pull-buoys, and dumbbells, according to each participant’s RPE on the Borg CR-10 scale.

**Table 1 pone.0320858.t001:** Aquatic-exercise program.

Type	Frequency and duration	Intensity	
		Week 1–4	Week 5–8
Aquatic exercise: aerobic, resistance, and flexibility training performed in water.	2 times per week. Session duration: 40–45 min (warm-up phase: 5 min, training phase: 30–35 min; and relaxation/cool-down phase: 5 min).	Warm-up phase:	Warm-up phase:
		Low-intensity aerobic exercise: walking forwards, sideways, and backwards. RPE: 3–4 (Borg CR-10 Scale).	Low-intensity aerobic exercise: walking forwards, sideways, and backwards. RPE: 3–4 (Borg CR-10 Scale).
		Training phase:	Training phase:
		Active range of motion exercises: spine, upper and lower limbs. RPE: 3–4 (Borg CR-10 Scale).	Active range of motion exercises: spine, upper and lower limbs. RPE: 3–4 (Borg CR-10 Scale).

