#### Land-exercise program.

This program will include specific land-based exercises (Table 2, guided by a physiotherapist. This intervention will include 8 sessions in 8 weeks, once a week, on a different day from the aquatic exercise program. Each session will last between 25 to 35 minutes and will be divided into two components: core stability exercises and stretching of the trunk and lower limbs [60]. Core stability exercises (15–20 minutes): these will consist of isometric exercises which contraction was maintained for 7–8 seconds, 8–12 repetitions, 1 set, with brief rest intervals of 3 seconds between repetitions and 30 seconds to 1 minute between exercises [60,61]. Exercises will include abdominal hollowing, side bridge (both sides), supine extension bridge, lower limb extension from prone (both sides), and alternate arm and leg raise from quadruped. Intensity will increase gradually by reducing rest time between exercises and increasing repetitions, based on participants’ performance. Participants will be instructed to contract and hold their abdominal muscles while maintaining normal breathing patterns [62]. Stretching exercises (10–15 minutes): participants will perform muscle stretching exercises, holding the maximum stretch for 30 seconds to 1 minute, and returning to the original position, followed by 5–10 seconds of rest. Each exercise will be repeated two to three times [63]. Stretches will target the hamstrings, iliopsoas, piriformis, and tensor fasciae latae. Participants will be instructed to minimize tension in other body muscles and maintain their usual breathing pattern during stretching [64–67].

**Table 2 pone.0320858.t002:** Land-exercise program

Type	Frequency and duration	Intensity	
		Week 1–4	Week 5–8
**Core stability exercises:** abdominal hollowing, side bridge (both sides), supine extension bridge, lower limb extension from prone (both sides), and alternate arm and leg raise from quadruped, performed in dry land.	1 time per week. Session duration: 25–35 min	**Isometric strength exercises:** contraction held for 7–8s, 8–10 reps, 1 set.	**Isometric strength exercises:** Contraction held for 9–10s, 10–12 reps, 1 set.
	(Core stability exercises: 15–20 min, and stretching exercises: 10–15 min).	Rest between reps: 3s	Rest between reps: 3s
		Rest between exercises: 1min.	Rest between exercises: 30s.
		RPE: 5–6 (Borg CR-10 Scale)	RPE: 6–7 (Borg CR-10 Scale)

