#### Randomization and Blinding.

Participants who meet eligibility criteria will be given an alphanumeric code to maintain data confidentiality and anonymity. Participants will be randomly assigned to either ALG or AG, with a 1:1 allocation. Randomization will be performed by the principal investigator using a block randomization method generated by a computer program to ensure equal sample sizes in both groups. The block size will not be disclosed to maintain concealment. Participants will be informed of their group allocation (ALG or AG) via telephone contact. The principal investigator will not be actively involved in the intervention, data collection or data analysis. Randomization will only be known to the physiotherapists responsible for the intervention and the principal investigator. The examiner will evaluate participants before the intervention and after 8 weeks of intervention, ensuring blinding to group allocation, and participants will be asked not to disclose this information to the examiner. Each intervention will have a physiotherapist responsible for its execution, who will be instructed not to reveal participants’ group allocation to other research team members. Both data collector and data analyst will be unaware of the participants’ group distribution and will also be considered blinded. Only the principal investigator will have full knowledge of the entire research flow.

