## Discussion

This study will investigate and compare the effectiveness of a water-based and land-based exercise program versus a solely water-based program on pain levels, functional disability, quality of life, lumbar mobility, and fear of movement in adults with CLBP. Additionally, an effort will be made to assess the effect of the cessation of exercise on the mentioned variables, 4 weeks after the end of the intervention. A minimum of 15 participants per group is expected to ensure the calculated sample power. However, a higher number of participants should be ensured, as it is known that approximately 50% of participants drop out within the first six months due to personal characteristics, environmental factors, or issues with the programs [55]. On the other hand, in order to maintain the methodological quality of the study, according to the Physiotherapy Evidence Database (PEDro) Scale, the variables should be measured at the end in more than 85% of the participants who were initially randomized [102].

Previously, an author conducted a RCT with 12 participants (6 in the experimental group and 6 in the control group) in which the effect of an aquatic exercise program (experimental) was compared with that of a land-based program (control) on the level of pain and mobility of the lumbar spine [41]. At the end of the interventions (6 weeks), no statistically significant differences were observed in pain (VAS) (ρ=0.523), nor in the lumbar spine mobility test (Modified-Modified Schober Test) (ρ=0.56). Another author also studied in a RCT the differences between a group of participants who engaged in an aquatic exercise program (experimental) and a group who engaged in a land-based program (control) with 65 individuals with LBP (32 in the experimental group and 33 in the control group) [42]. After 4 weeks of intervention, statistically significant differences were observed favoring the experimental intervention in the ODI score (ρ < 0.001) and in the physical function (ρ < 0.001) and physical performance (ρ < 0.001) domains of the SF-36 questionnaire. No statistically significant differences were found between the groups in rest pain, pain during movement, or nocturnal pain (VAS), in lumbar mobility test (Modified-Modified Schober Test), or in the remaining domains of the SF-36 questionnaire.

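### Excluding everyone below 80% attendance makes the only described comparison a per-protocol one, and the cut-off is not the same in the two arms

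*Protocol article*

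**What the plan says.** The Participant adherence section sets the rule, to be applied once the interventions have ended: "participants who do not achieve at least 80% of the total sessions will be excluded from data analysis". Attendance is scored 0 or 1 per session and covers both components: "Individual participation in each exercise session (both land and aquatic) will be recorded by the physiotherapist responsible for the intervention".

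The two arms have different numbers of sessions. Under Intervention: "The AG will conduct the aquatic exercise program, while the ALG will carry out both aquatic and land-based exercise programs". For the aquatic programme: "It will include 16 sessions, twice a week, over 8 weeks". For the land programme: "This intervention will include 8 sessions in 8 weeks, once a week, on a different day from the aquatic exercise program". AG therefore has 16 sessions and ALG has 24.

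The Statistical analysis section describes a 2×3 mixed ANOVA and names no analysis set. No section describes an analysis that keeps the participants removed by the 80% rule. The Participants section plans 15 per arm, with 15% added in each arm for possible dropouts.

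**The concern.** Attendance is observed after randomisation. A participant may stop coming because of pain, poor tolerance, an adverse event, lack of benefit, or because they feel better. Removing people on that basis means the groups compared are no longer the groups that were randomised, and baseline comparability is lost. This holds even if both arms lose equal numbers.

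The protocol itself says that poor adherence may affect the results, and its adverse-event section allows referral for treatment or rest. A participant who misses two full weeks is left with 12 of 16 (AG) or 18 of 24 (ALG), which is 75% in either arm, and is removed.

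Because the arms have different session totals, the same percentage also acts differently on each. With about 18 per arm, a few exclusions can change the result, and they use up a reserve that was sized for dropouts alone.

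**Working it through.** **Inputs from the protocol.** Sessions: AG 16; ALG 16 + 8 = 24. Threshold: 80% of total sessions. Sample size: effect size d = 1.079, alpha 0.05, power 80%, 15 per arm, plus 15% for dropouts. Attendance per session is not given, so it is an assumption below and is shown as a range.

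**1. The plan's own sample size.** Two-sample t test, two-sided alpha 0.05, noncentral t with 2n − 2 degrees of freedom and noncentrality d·√(n/2). At n = 15 power is 0.814; at n = 14 it is 0.785. So 15 per arm is the smallest n that reaches 80%, which reproduces the stated 30. (Sidedness is not stated; a one-sided test would need only 12 per arm, so two-sided is the variant that matches.)

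**2. The cut-off in each arm.**
- AG: 0.8 × 16 = 12.8, so 13 sessions (81.3%); 3 may be missed.
- ALG: 0.8 × 24 = 19.2, so 20 sessions (83.3%); 4 may be missed.

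A participant with all 16 aquatic sessions is always kept in AG. In ALG the same participant is removed with fewer than 20 − 16 = 4 of the 8 land sessions.

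**3. Share kept, assuming equal and independent per-session attendance p.** AG: P(X ≥ 13), X ~ Bin(16, p). ALG: P(X ≥ 20), X ~ Bin(24, p).

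| p | AG kept | ALG kept | Difference |
|---|---|---|---|
| 0.80 | 0.598 | 0.460 | 0.138 |
| 0.85 | 0.790 | 0.713 | 0.077 |
| 0.90 | 0.932 | 0.915 | 0.017 |
| 0.95 | 0.993 | 0.994 | −0.001 |

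**4. Two variations, both assumed.**
- Attendance clustered within persons (beta-binomial, intraclass correlation 0.1 to 0.3, mean 80% to 90%): the gap shrinks to about 2 to 7 percentage points.
- Land day attended less often (aquatic 90%, land 70%): 0.93 kept in AG against 0.63 in ALG.

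**5. The dropout reserve.** 15 × 1.15 = 17.25, so 18 per arm. Keeping 15 allows 18 − 15 = 3 losses per arm from all causes. At an assumed 85% attendance the rule alone leaves 18 × 0.790 = 14.2 in AG and 18 × 0.713 = 12.8 in ALG, before any dropout that is not already counted as poor attendance.

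**6. Power at d = 1.079, held fixed.** 18 per arm: 0.88. 15: 0.81. 14: 0.78. 13: 0.75.

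**7. How far the unequal cut-off could shift the contrast (illustration).** Suppose attendance is a normal latent variable with correlation r to the outcome, and each arm keeps its upper fraction k. The mean in that arm shifts by r·φ(z)/k SD, where z is the cut point and φ the normal density. With the retention rates of step 3 and r from 0.3 to 0.5, the difference between arms is 0.065 to 0.108 SD at 80% attendance, 0.034 to 0.056 at 85%, about 0.01 at 90%, and essentially nil at 95%. Both r and its sign are assumptions.

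**The case against.** The protocol works to keep attendance high: reminders, contact after two consecutive missed sessions, and modified versions of the aquatic exercises. If attendance reaches 90% to 95% in both arms, the unequal action of the cut-off is negligible, and independence between sessions overstates it. That stands, and it limits the size of the arm difference. It does not remove the selection on attendance. Nor is this a detail left to an unseen analysis plan, because the exclusion is stated outright and without qualification.

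The cut-off would act equally if total sessions meant aquatic sessions only, but attendance is recorded for land and aquatic sessions alike.

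A reader might infer more than the document supports:

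- *Analyst blinding is broken, because the rule needs each person's denominator.* The protocol says "Both data collector and data analyst will be unaware" of allocation, but not that the analyst applies the rule. The physiotherapists and the principal investigator know the allocation, and one of them could pass on a filtered, coded file.
- *The rule contradicts the completeness target in the Discussion.* That target is that "the variables should be measured at the end in more than 85% of the participants who were initially randomized". It concerns measurement; the rule concerns analysis. A participant can be measured and then left out.
- *The bias favours ALG.* That requires poor attenders to have worse outcomes. The document gives no such relation, and some may stop because they have improved.
- *The shift is 0.09 to 0.15 SD.* That needs about 10% of AG and 30% of ALG to be removed (r = 0.3 to 0.5), a split that equal attendance does not produce.
- *Dropout and under-attendance can be added together.* They overlap, since many who drop out during the eight weeks will also fall below 80%.

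**Conclusion.** The concern holds. As written, the only comparison described excludes randomised participants on attendance after randomisation and is therefore a per-protocol comparison. This rests on the text alone and needs no assumption about attendance.

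The unequal threshold, 13 of 16 against 20 of 24, is also certain. Its effect is not. Under equal, independent attendance the gap in retention runs from about 14 percentage points at 80% attendance to none at 95%. It is smaller with clustering within persons and larger if the extra land day is attended less. The size and direction of any bias cannot be fixed from the document.

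The effect on power is moderate: from 81% to 78% or 75% if 14 or 13 per arm remain, with d held at its planned value. The main reason to change the rule is the loss of the randomised comparison, not the loss of power.

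**What to change.** Replace the exclusion sentence under Participant adherence, before the data are analysed, with wording to this effect: the primary analysis includes all randomised participants in the arm to which they were allocated, regardless of attendance; M1 and M2 are sought from everyone, including those who stop attending; the set attending at least 80% of sessions is used only for a supplementary per-protocol analysis, with the denominator stated for each arm (16 in AG, 24 in ALG).

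The Data Collection section already implies that all enrolled participants complete the three assessments, so this adds no visit. Defining adherence separately for the aquatic and land components is optional. It would show better whether the combined programme was received, but it is a design preference and not a correction.

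The cost is a wording change and some effort to obtain follow-up from poor attenders. The estimated effect may be smaller than among good attenders only, so the power figures at d = 1.079 may be somewhat optimistic for the all-randomised analysis.

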### Statistical analysis

An inspection of the data will be made for missing values or univariate outliers. A priori power analysis through ${\text{G}}^{*}$Power (3.1.9.7) [96] and ANOVA repeated measures, within-between interaction will be use to determine the required sample size considering the following input parameters: (effect size *f* = 0.4; α err prob = 0.05; statistical power = 0.95) [97]. Data analyses will be performed using SPSS Statistics version 29.0 (SPSS Inc., IBM Company, Chicago, Illinois, USA). Descriptive statistics (mean ± SD) will be performed for all variables in the analysis. Assuming data normality, a 2×3 within-between interaction factorial ANOVA will be applied for intra and inter group comparisons. To control for Type I errors, multiple comparisons will be adjusted using the Bonferroni correction (i.e., alpha level divided by the number of tests) as suggested by several authors (e.g., Ho, 2014) [98].The magnitude of the global effect size will be calculated using Cohen’s effect size. The Cohen’s *d* effect size is categorized according to the following criteria: *d* = < 0.20 (small), 0.21–0.79 (medium) and > 0.80 (large) [99–101]. Significance level set at ρ
≤ 0.05. Full statistical analysis and results are expected to be completed in May 2025.

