Moreover, few authors have investigated the effects of cessation of exercise [45,46]. Mujika & Padilla [46] argue that detraining can be divided into two study periods: short-term, less than 4 weeks, and long-term, more than 4 weeks. Therefore, Toraman & Ayceman [47] found that after 4 weeks of interruption following a 9-week aerobic, strength, and flexibility training program, conducted 3 times a week, participants showed a reduction in performance levels on various functional tests, standing out the Chair Sit and Reach, compared to the end of the intervention, although the changes were not statistically significant. Thus, the impact of aquatic exercise, core stability exercise, and trunk and lower limb stretching cessation on individuals with CLBP remains unclear.

This trial aims to assess the effect of a combined aquatic and land-based exercise program compared to an aquatic program on pain, functional disability, and quality of life in adults with CLBP. Secondary objectives include investigating the effects on lumbar mobility and fear of movement, as well as the impact of training cessation on these variables 4 weeks after the end of the intervention. We hypothesize that combined aquatic and land-based exercise decreases significantly pain, and functional disability, and increases quality of life in adults with CLBP.

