### Participants

The study sample will consist of both gender Portuguese participants, over 18 years, with CLBP lasting three months or longer and with an intensity of 3 or higher on the visual analogue scale (VAS) at rest. Individuals who refuse to participate or do not provide informed consent will be excluded, as well as those with pain radiating to the lower limb, recent pregnancy or childbirth (less than 8 weeks ago) [50], ongoing physical therapy treatments, severe rheumatological, neurological, neoplastic, cardiovascular diseases, or other conditions that could prevent full participation in the intervention, a history of spinal surgery, inflammatory, infectious, or malignant spinal diseases, and psychiatric disorders that may affect adherence and symptom assessment [41–43].

The sample will be randomly divided into two groups: the experimental group, which will undergo the aquatic and land-exercise program (ALG), and the control group, which will perform the aquatic-exercise program (AG).

The required sample size was calculated using the G*Power software (3.1.9.4; Heinrich Heine University Düsseldorf, DE), based on a study with 65 participants by Dundar *et al*. [42] and corroborated by other studies [51–53]. The aim was to detect differences in pain intensity (VAS) between the aquatic exercise program group and the control group (land exercise), with an effect size of 1.079, α=0.05, and a power of 80%. The total sample size needed to achieve the objective will be 30 participants (15 in each group).

Thus, the study should start with an additional 15% of the planned sample size for each group to account for potential dropouts and as well as adopt cognitive-behavioral strategies to reduce dropout rates, such as setting flexible and participant-driven goals or providing positive and individualized feedback [54,55].

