#### Data Collection.

After enrollment, participants will complete three evaluation phases: before the intervention (M0), after the intervention (M1), and 4 weeks after the end of the intervention (M2). Data collection started in November 2024 and is expected to be completed in April 2025. During data collection, participants will start each data collection session by filling out the questionnaires (Oswestry Disability Index, MOS Short Form Health Survey 36 Item, and Tampa Scale of Kinesiophobia-13) and the Visual Analog Scale for pain at rest, during movement, and at night, which will take approximately 30 minutes. Following this, the physiotherapist responsible for the assessment will measure weight and height, and then assess lumbar spine mobility using the Modified-Modified Schober Test, taking the best of three measurements. To standardize data collection, each participant will be asked to stand barefoot on a paper where the outline of their feet will be drawn to ensure consistent positioning across all measurements. This procedure will be repeated three times, with a 30-second break between repetitions. Participants will be instructed to place their feet at hip-width apart and their upper limbs relaxed along the body in the test starting position [68,69]. Fig 2 shows the study design with key moments of the intervention and data collection.

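### The 2×3 ANOVA given for all objectives does not isolate the arm difference at the end of the intervention (M1): its interaction can be significant because of the secondary visit M2 alone

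*Protocol article*

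**What the plan says.** All references are to the protocol article.

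- **Aims (Introduction).** The main aim is the programme effect: "This trial aims to assess the effect of a combined aquatic and land-based exercise program compared to an aquatic program on pain, functional disability". The third outcome named there is quality of life. No visit is named. Cessation is placed lower: "Secondary objectives include investigating the effects on lumbar mobility and fear of movement, as well as the impact of training cessation on these variables", assessed 4 weeks after the programme ends.
- **Visits (Data Collection).** Assessments are "before the intervention (M0), after the intervention (M1), and 4 weeks after the end of the intervention (M2").
- **Sample size (Participants).** "The aim was to detect differences in pain intensity (VAS) between the aquatic exercise program group and the control group", with effect size 1.079, α = 0.05 and 80% power, giving 15 per arm.
- **Analysis (Statistical analysis).** The model is "Assuming data normality, a 2×3 within-between interaction factorial ANOVA", meant to serve comparisons both within and between the arms. After that, "multiple comparisons will be adjusted using the Bonferroni correction (i.e., alpha level divided by the number of tests"). Which comparisons are meant, and how many, is not said. The same section gives a second power specification for the within-between interaction (f = 0.4, power 0.95), without a resulting sample size.

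**The concern.** M2 is a secondary, off-treatment visit, and the Discussion poses the open question as which arm will be ahead when the intervention ends. Together these point to the M1 difference as the primary comparison. The stated model does not single it out.

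The group-by-visit interaction has two degrees of freedom and responds to any difference in profile over M0, M1 and M2. The group main effect averages the arm difference over all three visits, including baseline, where randomisation makes the expected difference zero. The follow-up comparisons could include the M1 difference, but nothing marks it as primary or says whether the interaction must first be significant.

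At stake is which result counts as success on the main aim. As written, a significant interaction, a significant main effect, or a pairwise difference at M1 or at M2 could each be presented as the answer once the data are known.

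**Working it through.** **Inputs from the protocol article.** n = 15 per arm, d = 1.079 SD, α = 0.05 (two-sided taken), three visits.

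**Assumptions not in the document.** SD 1 at each visit and an equal within-person correlation r between visits, with r = 0.3, 0.5 and 0.7.

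**1. The stated sample size.** For a two-sample t-test with 28 df, the non-centrality is 1.079/√(2/15) = 2.955 and power is 0.814. Solving for 80% gives 14.51, so 15 per arm. The stated 30 is reproduced as a single two-group comparison.

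**2. Formulas.** Let the arm differences at M0, M1 and M2 be (0, δ1, δ2).
- Interaction: F with 2 and (30 − 2) × 2 = 56 df, λ = (n/2) × Σ(δt − mean δ)² / (1 − r).
- Group main effect: t with 28 df, difference (0 + δ1 + δ2)/3, variance of a patient's mean (1 + 2r)/3.
- M0-to-M1 change: t with 28 df, difference δ1, variance 2(1 − r).
- M1 adjusted for M0 (ANCOVA): t with 27 df, difference δ1, residual variance 1 − r². Values are from simulation (20,000 trials per case).

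**3. Difference at M2 only (δ1 = 0, δ2 = 1.079).** Σ = 1.079² × 2/3 = 0.776, so λ = 7.5 × 0.776/(1 − r) = 8.32, 11.64 and 19.40. The interaction rejects with probability 0.71, 0.85 and 0.98. Every direct M1 test rejects at 0.05. Simulation agrees to within about one percentage point.

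**4. A true M1 effect of 1.079 SD.** Power at r = 0.3 / 0.5 / 0.7:

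| Part of effect left at M2 | Interaction | Group main effect | M0-to-M1 change | M1 adjusted for M0 |
|---|---|---|---|---|
| None | 0.71 / 0.85 / 0.98 | 0.26 / 0.21 / 0.19 | 0.67 / 0.81 / 0.96 | 0.83 / 0.90 / 0.975 |
| Half | 0.58 / 0.73 / 0.92 | 0.50 / 0.42 / 0.36 | 0.67 / 0.81 / 0.96 | 0.83 / 0.90 / 0.975 |
| All | 0.71 / 0.85 / 0.98 | 0.74 / 0.64 / 0.57 | 0.67 / 0.81 / 0.96 | 0.83 / 0.90 / 0.975 |

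If a fraction x of the effect remains at M2, the interaction's non-centrality is proportional to 1 + x² − (1 + x)²/3. This is 0.667 at x = 0, 0.50 at x = 0.5 (the minimum) and 0.667 at x = 1. Half retention is therefore the interaction's worst case between full fade and full persistence.

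**5. Reaching M1 through the pairwise comparisons.** If the arms are compared at each of the three visits, α = 0.05/3 = 0.0167. With the same non-centrality of 2.955, power at M1 is 0.66. One third of the error rate goes to baseline. Three comparisons is an assumption, since the number is not stated.

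**The case against.** The strongest reply has four parts.

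- **The ANOVA is not the whole plan.** A reader might infer that it is the only test and that the M1 question goes untested. The documents do not support that: the model is said to serve comparisons between groups, and adjusted multiple comparisons follow. An M1 comparison is available; it is not designated as primary.
- **The interaction is a legitimate target and need not lose power.** Averaging over visits describes only the group main effect, which the article never presents as the test of its aim; the interaction compares profiles. A reader might infer that any fading effect is diluted. That fails at both ends: with full fade or full persistence the interaction slightly exceeds the unadjusted change contrast (0.85 v 0.81 at r = 0.5). The article also gives a separate 0.95 power specification for the interaction. Its inputs need 26, 18 or 12 participants at r = 0.3, 0.5 or 0.7 under the G*Power default, although 34 at r = 0 and 52 under the software's other effect-size option. How that fits with the 80% calculation is a separate matter.
- **No baseline test is listed.** A reader might infer that arms will be compared at M0. The article does not say so; this is a risk of the open-ended wording.
- **M1 as primary is inferred, and an article may leave contrasts to an analysis plan.** Both are fair. A plan not shown may name the contrast. The article is not silent, however: it fixes an omnibus model for all objectives, and a better-targeted test using data already collected can replace it.

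The pattern with no difference at M1 and a large one at M2 is also an extreme case. It shows what the test responds to and is not a forecast.

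**Conclusion.** The point holds in this form: the stated omnibus model mixes the primary M1 question with the secondary M2 question, and no contrast is fixed as the answer to the main aim. The interaction would reject in about 71% to 98% of trials on an M2-only difference of 1.079 SD. The group main effect has only 19% to 26% power for an effect confined to M1. Comparing arms at three visits with Bonferroni adjustment would leave about 66% power at M1, short of the planned 80%.

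The main harm is an ill-targeted test. Lost power is secondary and depends on the scenario: against the baseline-adjusted M1 test, the interaction is clearly weaker with half retention (0.58 / 0.73 / 0.92 v 0.83 / 0.90 / 0.975). With full fade or full persistence it is weaker at r = 0.3 and 0.5 and about equal at r = 0.7. These figures rest on equal correlations of 0.3 to 0.7, constant SD and 15 analysed per arm. That M1 is the primary time point is inferred from the ordering of the aims.

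**What to change.** In the Statistical analysis section:

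1. Name the between-arm difference at M1, adjusted for the M0 value (ANCOVA or the equivalent mixed-model contrast), as the primary one-degree-of-freedom test for each primary outcome.
2. Make the between-arm difference at M2 a separate, secondary contrast for the cessation objective.
3. State that neither the omnibus interaction nor the group main effect is the primary test or a gate to it.
4. List the comparisons that the Bonferroni correction covers, and keep any between-arm comparison at M0 out of that family.

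This needs no extra participants or measurements, only revised wording, settled before outcomes are seen by arm. The price is that a difference appearing only at M2 is reported as a secondary result.
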